### Measurement time points

Independent variables (predictors) will be measured at two points: within 7 days of the first-ever stroke onset and at 1st month post-stroke. Dependent variables (outcomes) will also be assessed at two points, at the 1st and 3rd months post-stroke. (Table 1)

**Table 1 tbl0001:** Time points of predictor and Outcome measure assessment.

Measures		Within 7th day	1st Month	3rd Month
**Independent Variable** (Predictor)	sEMG recording of Upper limb muscles	**✔**	**✔**	
	sEMG recording of lower limb muscles	**✔**	**✔**	
**Dependent Variable** (Outcomes)	FMA-UE		**✔**	**✔**
	ARAT		**✔**	**✔**
	FMA-LE		**✔**	**✔**
	FAC		**✔**	**✔**
	10mWT		**✔**	**✔**
	Mini-BEST		**✔**	**✔**
	SIS		**✔**	**✔**

**Abbreviation:** FMA-UE, Fugl Meyer Assessment-Upper Extremity; ARAT, Action Research Arm Test; FMA-LE, Fugl Meyer Assessment-Lower Extremity; FAC, Functional Ambulation Category; 10mWT, 10-meter Walk Test; SIS, Stroke Impact Scale.

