## Abstract

Stroke is a leading cause of long-term disability, resulting in motor impairments that significantly affect the quality of life. Predicting motor recovery is particularly difficult for people with severe motor impairment early after stroke. Traditional assessments are limited in terms of residual muscle activity, which is crucial for tailoring rehabilitation interventions. Incorporating surface electromyography (sEMG) assessment can provide a deeper understanding of motor recovery potential in severe motor impairment. This prospective cohort study aims to develop a TRIPOD-compliant prediction model to examine whether sEMG amplitude recorded from five upper and four lower extremity muscles within the first week of stroke could predict motor recovery at 3 months post-stroke. This prospective study will include 76 participants between the ages of 18–80 years presenting first-ever anterior or middle cerebral artery stroke resulting in a severe motor impairment within the first week of stroke onset. In addition to sEMG recording to evaluate muscle activity, participants will undergo a comprehensive clinical assessment of motor functions and activity at the 1st and 3rd months following stroke onset. Multivariate regression analyses will be used to determine associations between sEMG metrics and recovery outcomes.

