Despite its advantages, the application of sEMG in early stroke recovery prediction is still unexplored in clinical practice. Currently, the majority of applications focus on biofeedback or rehabilitative monitoring rather than prognostic modelling. The lack of established procedures, limited awareness among clinicians, and differences in signal interpretation may all contribute to this underutilization. Therefore, a thorough examination of the prognostic potential of sEMG is needed, especially during the acute stage of stroke. To bridge this gap, we aimed to develop a prediction model for people with severe motor impairment after stroke, employing surface electromyography to analyse whether the amplitude of muscle activity recorded from upper limb muscles such as anterior deltoid, middle deltoid, long head of biceps brachii, long head of triceps brachii and extensor carpi radialis and lower limb muscles such as tibialis anterior, medial head of gastrocnemius, rectus femoris, and biceps femoris within the first week of stroke could predict upper and lower extremity motor recovery and activity capacity of the upper extremity, postural balance, and walking at 3 months post stroke. These muscles were selected because they represent key proximal and distal muscle groups commonly involved in upper and lower extremity functions, balance and walking functions after stroke [24,25]. We hypothesized that greater sEMG amplitude recorded within the first week post-stroke, reflecting detectable voluntary muscle activity in the absence of visible movement, would be positively associated with upper and lower extremity motor recovery, upper extremity activity capacity, postural balance, and walking ability at 3 months post-stroke.

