## Procedure

All patients admitted with acute stroke to the study center during the recruitment period will be consecutively screened within the first week of stroke onset for eligibility. A screening log will be maintained to document the number of patients screened, included, excluded (with reasons), and those who decline participation. Information recorded in the screening log will inform the final participant numbers, as summarised in the study flow diagram (Fig. 1). Patients who fulfil the inclusion criteria will be requested to participate in the study. The measurements will be recorded the next day after the consent for participation. Raw sEMG signals will be collected from the paretic side at two time points—within 7 days and again at 30 days after stroke onset and processed via Lab Chart 8.1.30 software. The raw data (%Maximal Voluntary Contraction) will be normalized by the mean Root Mean Square (RMS) /max RMS X100, which will be used for analysis. Mean RMS will be computed for each 10-second trial during task execution and then averaged across trials. The following clinical assessments will be collected at the 1st and 3rd months after stroke onset: Fugl Meyer Assessment (FMA), Action Research Arm Test (ARAT), Functional Ambulation Category (FAC), 10-meter Walk Test (10MWT), Mini BEST, and Stroke Impact Scale (SIS)Version 3.0. During the hospitalization phase, all the measurements will be performed in a quiet room next to the stroke unit. During follow-up, a recording will be performed at the physiotherapy department. To minimise detection bias, assessors conducting clinical outcome assessments at the 1st and 3rd month follow-ups will be blinded to baseline sEMG measurements. Assessments will be performed by a licensed neurophysiotherapist with formal training in standardised stroke outcome measures. The investigator responsible for sEMG acquisition will be a neurophysiotherapist trained in sEMG recording, will not be involved in outcome assessments, and will remain blinded to all follow-up outcomes.

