## Bias

All outcome assessments will be conducted using standardized, validated methods by trained assessors to minimize measurement error and information bias. Outcome assessors will be blinded to baseline predictor data to further minimize observer bias. To reduce attrition bias, we will employ reminders and flexible scheduling to collect follow-up data at all scheduled time points for each participant. Multiple time points will be used to gather data in order to capture longitudinal changes and increase the robustness of predictive modelling.

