## Statistical methods and analysis

The data will be analysed using R Studio. The normality of the distribution will be verified via the “Kolmogorov‒Smirnov test”. If the data are normally distributed, they will be presented as the mean ± SD; if they are not normally distributed, they will be presented as the median and interquartile range. Categorical variables will be presented as frequencies and percentages, or as medians and interquartile ranges. Spearman/Pearson correlation coefficients will be applied to all predictors and outcomes. Candidate predictors will be specified by using Penalised regression methods (elastic net) for model development to achieve coefficient shrinkage and reduce overfitting.

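### The 1-month sEMG is labelled a predictor alongside the first-week sEMG, so as written it could enter a model meant to predict 3-month recovery from the first week

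*Protocol article*

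**What the plan says.** **The question.** The Abstract asks whether sEMG amplitude recorded "within the first week of stroke could predict motor recovery at 3 months post-stroke". The aim in the Background asks the same of amplitude recorded "within the first week of stroke could predict upper and lower extremity motor recovery", and of arm activity capacity, balance and walking, at 3 months. The hypothesis begins "We hypothesized that greater sEMG amplitude recorded within the first week post-stroke". The sEMG analysis section treats early amplitude against later recovery as the primary association.

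**The predictors.** Under Procedure, sEMG is recorded "within 7 days and again at 30 days after stroke onset". The Measurement time points section then states: "Independent variables (predictors) will be measured at two points: within 7 days of the first-ever stroke onset and at 1st month post-stroke". Table 1 ticks both times in the rows headed as independent variables.

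**The modelling.** The Bias section says: "Multiple time points will be used to gather data in order to capture longitudinal changes and increase the robustness of predictive modelling". In turn, the section headed Statistical methods and analysis says: "Spearman/Pearson correlation coefficients will be applied to all predictors and outcomes". It then hands the candidate predictors to an elastic net, with no limit by time point.

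**The outcomes.** All outcomes are assessed at 1 and 3 months. The primary endpoint is FMA at 3 months.

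**Blinding.** Under Procedure, outcome assessors at both follow-ups "will be blinded to baseline sEMG measurements". The person who records sEMG takes no part in outcome assessment and stays blinded to follow-up outcomes.

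**The concern.** A prognostic model has a time origin, and everything it uses must be known at that time. Here the stated origin is the first week. The Specifications table gives the purpose as guiding individual rehabilitation intensity and goal setting for people with severe deficits in the acute phase.

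The 1-month recording does not exist at that origin. It is taken after several weeks in which recovery may already have occurred, and closer to the 3-month endpoint. If it enters the model, two things follow. The model cannot be applied in week 1. Its discrimination, calibration and net benefit then describe prediction from 1 month, partly reflecting recovery already achieved, and not prediction from week 1.

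For 1-month outcomes the label fails in a different way. Predictor and outcome share the same nominal time point, so any association is cross-sectional.

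The planned bootstrap and leave-one-out validation would not reveal the problem. They resample whatever predictor set is supplied, so they address overfitting and not the timing of the information.

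**Working it through.** **1. The passages side by side.**

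| Section | Time of sEMG | Role given |
|---|---|---|
| Abstract; Background (aim, hypothesis) | First week | Predictor of 3-month recovery |
| sEMG analysis | Early | Primary association |
| Measurement time points; Table 1 | Within 7 days and 1 month | Predictor, both |
| Bias | Multiple time points | Supports predictive modelling |
| Statistical methods and analysis | Not stated | All predictors correlated with outcomes; elastic net for candidates |

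The first two rows fix the origin at week 1. The third widens the predictor set to 1 month, and the last two do not narrow it again. No section makes the 1-month sEMG descriptive, gives it a landmark model of its own, or bars it from the 3-month model.

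**2. The plan's own figure.** The only correlation in the document is r = 0.6, with precision d = 0.20, under Sample size estimation. The formula reproduces: 1.96² × (1 − 0.6²) / 0.20² = 3.8416 × 0.64 / 0.04 = 61.47, given as 61. Then 61 / 0.80 = 76.25, given as 76. The present point does not depend on this result.

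**3. Illustration of what could change.** Let W be the week-1 sEMG, M the 1-month sEMG and Y the 3-month outcome.

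Assumptions:
- r(W,Y) = 0.6. This borrows the sample-size value, which the document does not tie to this particular pair.
- r(M,Y) from 0.6 to 0.8. Not in the document.
- r(W,M) from 0.5 to 0.8. Not in the document.

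With W alone, R² = 0.6² = 0.36 and the standardised coefficient of W is 0.60. With both:

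R² = [r(W,Y)² + r(M,Y)² − 2·r(W,Y)·r(M,Y)·r(W,M)] / [1 − r(W,M)²]

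β(W) = [r(W,Y) − r(M,Y)·r(W,M)] / [1 − r(W,M)²]

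| r(M,Y) | r(W,M) | R² with both | β(W) |
|---|---|---|---|
| 0.6 | 0.5 | (0.72 − 0.36)/0.75 = 0.48 | (0.60 − 0.30)/0.75 = 0.40 |
| 0.6 | 0.8 | (0.72 − 0.576)/0.36 = 0.40 | (0.60 − 0.48)/0.36 = 0.33 |
| 0.8 | 0.5 | (1.00 − 0.48)/0.75 = 0.69 | (0.60 − 0.40)/0.75 = 0.27 |
| 0.8 | 0.8 | (1.00 − 0.768)/0.36 = 0.64 | (0.60 − 0.64)/0.36 = −0.11 |

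Over this grid R² rises from 0.36 to between 0.40 and 0.69. The coefficient for week-1 sEMG falls from 0.60 to between 0.40 and −0.11. The gain may be small or large, but none of it is available in week 1.

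**The case against.** The strongest reply is that no sentence puts the 1-month sEMG into the 3-month model. Measurement time points and Table 1 form a schedule, not a model specification. Every passage that defines the question says first week or early, and the Model development and validation section promises prespecified predictors. Which recording enters which model may be settled in an analysis plan not shown here. The Bias sentence can also be read as referring to repeated outcomes, and the correlation step is separate from the elastic net.

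Much of this stands. A reader might infer that the protocol has committed to using the 1-month sEMG in the 3-month model. It has not; it only leaves that open. What does not fall away is the label itself. The article says in text and in its table that the 1-month recording is a predictor. That is a statement in conflict with the aim, not a detail left for later.

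Three further inferences should be resisted:

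- **That the 1-month recording is an unblinded predictor.** Procedure separates the sEMG investigator from outcome assessment and blinds that person to follow-up outcomes. All that can be said is that the assessors' blinding is worded for baseline sEMG only.
- **That there are 18 sEMG candidates.** Nine muscles at two times would give 18, but the protocol never says that all are candidates. Nine at one time already exceeds the anticipated budget of about 7, so that is a separate matter.
- **That 1-month sEMG has no place as a predictor.** It precedes the 3-month endpoint and is legitimate in a model whose origin is 1 month.

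**Conclusion.** The concern holds as a conflict between passages with a conditional consequence. The aim, the hypothesis and the primary association concern first-week sEMG, while the predictor definition includes the 1-month sEMG and the analysis text does not exclude it. If the definition is followed literally, the resulting model is unusable in week 1 and its performance does not answer the stated question. For 1-month outcomes, the 1-month sEMG is concurrent whatever its correlations.

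The size cannot be taken from the document. The R² range of 0.40 to 0.69, against 0.36, rests on assumed correlations and shows only that the effect could run from slight to large. It also cannot be assumed that the elastic net would favour the 1-month recording, since that depends on the same unknown correlations.

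The matter should be settled before analysis. If the time point is chosen once the data are seen, the model reported as early prediction could rest on whichever recording performs better.

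**What to change.** Reconcile Measurement time points, Table 1, Bias, and Statistical methods and analysis so that they say the following:

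- Only sEMG recorded within 7 days of onset is a candidate predictor in the primary 3-month model, and in any model reported as early prediction.
- The 1-month sEMG is used descriptively (for example, to show change), or in a separately labelled secondary landmark model with origin at 1 month and outcome at 3 months.
- The 1-month sEMG is not used as a predictor of 1-month outcomes.

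In Table 1, label the 1-month sEMG ticks accordingly.

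Optionally, extend the assessors' blinding under Procedure from baseline sEMG to all sEMG. This is a tidying of wording, since the recorder is already separated from the assessors.

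The cost is wording only. The sample size stays at 76 and no visit or recording is lost. The price is that headline performance may be lower than that of a model which borrows the 1-month data.

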### Background variables

To describe the study population, baseline background variables, including demographic and clinical characteristics, will be recorded in accordance with core recommendations for standardized reporting in sensorimotor stroke recovery and rehabilitation trials [39].

## Quality control

### sEMG signal acquisition

Contraction tasks are standardised across participants. Visual inspection will be performed to identify artefacts related to movement, signal dropout, or excessive noise. Trials with a signal-to-noise ratio below 20 dB or excessive artefacts will be rejected. In such cases, recordings will be repeated where feasible; otherwise, affected trials will be excluded from analysis. Baseline noise levels will be checked before each recording session. Crosstalk will be minimised through SENIAM-based electrode placement, alignment with muscle fiber direction, and single-muscle task execution. All sEMG recordings will be conducted by a trained physiotherapist experienced in sEMG acquisition, following a predefined standard operating protocol, and supervised by an investigator team with over 20 years of experience in sEMG and neurorehabilitation research.

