In this context, surface electromyography (sEMG) may be a promising alternative. It is an objective method that offers real-time data on muscle activity in terms of timing, location, contraction intensity [[18], [19], [20]] and can also identify subtle neuromuscular signals that will not be detected during a traditional clinical examination [21]. sEMG has the benefit of being able to monitor muscle activity even in the absence of perceptible or obvious movement [22] which is especially useful for evaluating patients with severe motor impairments and could lead to earlier and more precise prognosis [23]. Although the precise neurophysiological mechanisms underlying these early sEMG signals are not fully established, existing evidence have demonstrated measurable muscle activity through sEMG during acute care in patients classified as flaccid through conventional clinical assessment [23]. This ability strongly relates to the current study's goal, which is to investigate the prognostic value of early sEMG signals in forecasting functional outcomes and motor recovery.

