## Participants

We will include individuals aged 18–80 years, of any sex, with a first-ever ischemic or haemorrhagic stroke affecting the middle cerebral artery (MCA) or anterior cerebral artery (ACA). Recruitment will occur within seven days of stroke onset, and individuals reporting a Shoulder Abduction and Finger Extension (SAFE) score of <5(0–4) or knee extensor strength of <3/5 on the Medical Research Council (MRC) strength grade within this period will be included. Only those who are medically stable and able to follow simple commands will be included. The exclusion criteria will be individuals with a history of bilateral clinical strokes; those admitted more than seven days after stroke onset; patients who had undergone surgical interventions such as craniotomy or craniectomy; and individuals with pre-existing neurological or musculoskeletal disorders affecting motor functions.

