## Missing data

We will make every effort to ensure completeness of follow-up data at respective time points. In cases where data is missing, multiple imputation methods will be employed to facilitate comprehensive data analysis. Missing data in predictors and outcomes will be handled using multiple imputations by chained equations (MICE), under the assumption that data are missing at random. The imputation model will include all candidate predictors, outcome variables, and relevant auxiliary variables (such as age, baseline motor severity, stroke type, and time from stroke onset to assessment) to preserve observed associations. Twenty imputed datasets will be generated, and estimates will be pooled using Rubin’s rules.

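### The 20 dB rejection rule does not separate a poor recording from a clean recording of a weak or silent muscle, so it can remove the low end of the signal under study

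*Protocol article*

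**What the plan says.** All places are in the Protocol article.

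- **Quality control, sEMG signal acquisition.** "Trials with a signal-to-noise ratio below 20 dB or excessive artefacts will be rejected". What follows rejection is also fixed: "In such cases, recordings will be repeated where feasible; otherwise, affected trials will be excluded from analysis".
- **Background.** The case for sEMG is that it "can also identify subtle neuromuscular signals that will not be detected during a traditional clinical examination", and that earlier work has "demonstrated measurable muscle activity through sEMG during acute care in patients classified as flaccid". The hypothesis is that larger amplitude, "reflecting detectable voluntary muscle activity in the absence of visible movement", goes with better recovery.
- **Participants.** Entry requires a "Shoulder Abduction and Finger Extension (SAFE) score of <5(0–4) or knee extensor strength of <3/5", so a limb with no voluntary activity at all is eligible.
- **Electrode placement & task instructions; Procedure.** Each muscle has three 10-second trials. Mean RMS is taken per trial and averaged over trials. The analysed value is mean RMS divided by maximum RMS, times 100.
- **Missing data.** Missing predictors and outcomes go to chained-equation multiple imputation with 20 datasets, "under the assumption that data are missing at random".

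No section shown gives a rejected low-signal trial a zero, a floor or a category of its own.

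**The concern.** A low signal-to-noise ratio has two causes. Either the noise is high, which is a fault of the recording, or the muscle produces little signal, which is a finding about the patient. The rule treats both alike. Artefact, dropout and excessive noise are already looked for by visual inspection, so what the ratio criterion adds falls partly on clean recordings of weak muscles.

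The hypothesis is that more activity predicts more recovery, so faint or absent activity is the informative low end of the predictor. If those trials are discarded, the contrast between some activity and none is thinned out, the range of the predictor is narrowed, and the association with recovery is likely to be understated. The missing-data method would then rest on an assumption that the rejection rule itself undermines.

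**Working it through.** **1. What 20 dB requires.** The article does not define the ratio, so I take SNR = 20·log10(task RMS / baseline-noise RMS).

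| Task RMS / noise RMS | SNR (dB) | Outcome |
|---|---|---|
| 1 (no voluntary activity) | 0.0 | rejected |
| 2 | 6.0 | rejected |
| 3 | 9.5 | rejected |
| 5 | 14.0 | rejected |
| 10 | 20.0 | at the limit |

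Under any definition with the muscle signal in the numerator, an inactive muscle fails. Repeating the trial can cure technical noise but not an absent signal.

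**2. What then happens to the predictor.** There are three trials per muscle.
- Some fail: the average uses only the stronger trials and is biased upward. Nothing is imputed.
- All fail, repeats included: no value exists for that muscle. The only route the article gives for a missing predictor is imputation under missing at random. Here the value is missing because the activity was low.

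**3. Size among retained values.** From the sample-size section I take r = 0.6 and n = 61, which reproduces: 1.96² × (1 − 0.6²) / 0.2² = 61.46. Two assumptions are mine: the predictor is normal and rises with activity, and the lowest share p is rejected.

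With c the p-quantile of the standard normal and λ = φ(c)/(1 − p), the retained variance is v = 1 + cλ − λ². The retained correlation is r′ = r√v / √(r²v + 1 − r²).

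| Rejected share p | v | r′ | r′² | Observed of 61 |
|---|---|---|---|---|
| 0% | 1.00 | 0.60 | 0.36 | 61 |
| 5% | 0.81 | 0.56 | 0.31 | 58 |
| 10% | 0.71 | 0.53 | 0.29 | 55 |
| 30% | 0.49 | 0.47 | 0.22 | 43 |
| 50% | 0.36 | 0.41 | 0.17 | 31 |
| 70% | 0.26 | 0.36 | 0.13 | 18 |

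**4. Does imputation repair it?** These are complete-case figures, so imputation was simulated separately: n = 61, r = 0.6, 1,000 repetitions and 20 imputations from the outcome and one auxiliary variable, correlated 0.4 with each (assumed). With 10%, 25%, 50% and 70% rejected, the mean correlation after imputation was 0.55, 0.51, 0.43 and 0.36. The rejected values truly averaged −1.76, −1.27, −0.80 and −0.50 SD, but were imputed at −0.42, −0.01, +0.50 and +0.92 SD. Imputation recovers little, because it fills the gap from active muscles.

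**5. Would keeping the trials on the planned scale work?** The analysed value is mean RMS / max RMS × 100, and maximum RMS is not defined. If it is the largest 20-ms epoch of the same trial, simulated pure noise (10 s at 1000 Hz, band-passed) scores about 65%. A silent muscle would not enter as a low value.

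**The case against.** The strongest reply has five parts.

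- **Scale.** The predictor is a mean/max ratio, not raw amplitude, and a weak muscle can score high on it. This stands. The figures above hold only for a predictor that rises with activity, as the hypothesis supposes. It also means that simply keeping the trials as low values on the planned scale would fail.
- **Imputation.** A reader might infer that the protocol orders low-signal recordings to be imputed. It does not say so. This follows from combining two sections, and applies only where all of a muscle's trials fail.
- **Frequency.** Entry is by arm score or knee strength, so many participants may have one less affected limb, and arm scores of 1 to 4 imply some strength. Low rejection rates in many of the nine muscles are possible, and at 5% the loss is small (0.56 against 0.60).
- **Imputation model.** It includes outcomes, the other predictors and baseline motor severity, which carry some information about weak muscles. That softens the problem but does not make the data missing at random.
- **Documents not shown.** The recording procedures and operating protocol may define the ratio or score silent muscles. That is possible, but the rule as printed makes no exception. The planned sensitivity analyses on signal processing are conditional on feasibility and name neither the threshold nor the missing-data assumption.

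**Conclusion.** The point stands in limited form. As written, the rule rejects clean recordings of weak or silent muscles together with bad recordings, which conflicts with the study's stated target and population. The direction is clear: averages are biased upward when some trials fail, and predictors are missing for a reason tied to their own value when all fail.

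The size is not known. Under the stated assumptions the retained correlation lies between 0.56 (5% rejected) and 0.36 (70% rejected), against 0.60. Both ends rest on assumed rejection rates and on the tenfold reading of 20 dB.

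A reader might go further and conclude that the model will be unusable in flaccid patients, or that the lower end of the analysed predictor is certain to disappear. The documents support neither. Rejection rates are not given, some limbs will give strong signals, and on the mean/max scale low activity does not necessarily mean a low value.

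**What to change.** 1. Reject trials on technical grounds only: baseline noise above a prespecified limit, dropout or artefact. State how the signal-to-noise ratio is calculated if it is still reported.
2. Keep technically clean trials below 20 dB as observed data. Code them as a no-detectable-activity category, or as a floor on absolute, baseline-referenced RMS. Do not place them on the mean/max ratio.
3. Do not send these trials to imputation. Reserve imputation for recordings lost for technical reasons.
4. Report, per muscle, the share of clean trials below 20 dB, and run a sensitivity analysis with and without them.

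The cost is a short change to the quality-control text and a short addition on predictor coding. Values near the floor will be noisier. The change should precede further recording, because discarded trials may not be recoverable.
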